#### Other Secondary Efficacy Endpoints

1. Hemoglobin concentrations at 36-38 weeks of gestation;
2. Occurrence at birth of a neonate with congenital abnormalities;
3. Occurrence of a perinatal or neonatal deaths;
4. Birth weight of the live-borne neonate (singleton);
5. Number of episodes of symptomatic malaria per subject anytime from first IPTp dose administration to delivery;
6. Occurrence of a subject requiring additional treatment for malaria during the study period following the first dose (diagnosed based on clinical presentation and/or lab test results);
7. Occurrence of peripheral parasitemia at 36-38 weeks of gestation;
8. Occurrence of peripheral parasitemia at delivery;
9. Occurrence of cord blood parasitemia at delivery;
10. Occurrence of STIs including *T. pallidum*, *N. gonorrhoeae*, *C. trachomatis* during the study period following first dose (diagnosed based on clinical presentation prior to Week 36-38 and/or lab test results between Week 36-38);
11. Occurrence of a positive result for *C. trachomatis* infection at 36-38 weeks of gestation (diagnosed based on lab result);
12. Occurrence of a positive result for *N. gonorrhoeae* infection at 36-38 weeks of gestation (diagnosed based on lab result);
13. Occurrence of a positive result for *T. pallidum* test at 36-38 weeks of gestation (diagnosed based on lab result);
14. Occurrence of a *T. vaginalis* infection at 36-38 weeks of gestation (diagnosed based on lab result);

15. Occurrence of bacterial vaginosis at 36-38 weeks of gestation (diagnosed based on lab result);
16. Occurrence of ophthalmia neonatorum (diagnosed based on lab test results) in the neonate;
17. Occurrence of bacterial infections including pneumonia and other lower respiratory tract infections anytime from first IPTp dose administration to delivery;
18. Occurrence of pre-eclampsia from Week 20 to delivery;
19. Occurrence of nasopharyngeal swabs positive for macrolide resistant and penicillin resistant *Streptococcus pneumoniae* at baseline, at Day 28 (window Day 28 - Day 42) post delivery, and at about 6 months following last IPTp course. This test will be done in about 600 subjects each from the AZCQ and SP arms from two or more sites.

### **Safety Endpoints**

Safety and tolerability will be assessed by spontaneously reported adverse event reports, vital signs, physical examination, laboratory tests including hemoglobin and urine test for glucose and protein, and adverse pregnancy outcomes for mothers and by the general physical examination for the neonates through Day 28 (window Day 28 to Day 42) post delivery.

### **Outcome Research Endpoints**

To assess health economic impact from the health system and provider perspective, as measured by in-hospital and out-of-hospital healthcare utilization for the newborn/infant and the mother consumed due to low birth weight, infections and health complications. The endpoints will include:

1. Number of times a newborn/infant is taken to a local health clinic/physician's office/outpatient hospital clinic including Emergency Room (without having to be admitted) during the first 28 days (window Day 28 - Day 42) of life to attend to a health complication and the primary reason for visit;
2. Number of times a newborn/infant is admitted to a hospital during the first 28 days (window Day 28 - Day 42) of life, including length of hospital stay;
3. Number of times a mother is taken to a local health clinic/physician's office/outpatient hospital clinic including Emergency Room (without having to be admitted) from the time of the administration of the first dose of IPTp through Visit 6 on Day 28 (window Day 28 - Day 42) post delivery for treatment (or follow up) of Anemia, Malaria, STD or other complications and primary reason for the visit;
4. Number of times a mother is admitted to a hospital from the time of the administration of the first dose of IPTp through Visit 6 on Day 28 (window Day 28 - Day 42) post delivery, including length of stay in hospital.

### 3. STUDY DESIGN

This is a Phase 3, open label, randomized, parallel group study that will compare the efficacy of IPTp regimens of AZCQ and SP in asymptomatic pregnant subjects enrolled during second trimester of pregnancy. Approximately half of the subjects will be primigravidae and secundigravidae pregnant women since they have a higher risk for suboptimal pregnancy outcomes due to malaria. They will be randomized to receive either AZCQ or SP after informed consent is obtained (and assent if applicable) and inclusion/exclusion criteria are determined to have been met. Each subject will receive three IPTp courses of AZCQ or SP during ANC visits at 4 - 8 week intervals. The first treatment course will be administered during the second trimester (14-26 weeks of gestation as confirmed by ultrasound). The last treatment course should be given to subjects prior to or during 36 weeks of gestation. Subjects should be followed up at delivery or within 2 days of subject reporting home delivery (report within 24 hours of delivery), and on Day 28 (window: Day 28 to Day 42) post-delivery. Long lasting insecticidal-treated bednets (LLINs) will be given to all subjects on Day 0 of the study with the instructions to use them; the installation of LLINs will be verified during the first home visits of Treatment Course 1 by fieldworker(s).

### 4. SUBJECT SELECTION

This study can fulfill its objectives only if appropriate subjects are enrolled. The following eligibility criteria are designed to select subjects for whom protocol treatment is considered appropriate. All relevant medical and non-medical conditions should be taken into consideration when deciding whether this protocol is suitable for a particular subject.

Subjects who fail to meet the selection criteria for the study will be referred to the appropriate physician for receiving standard ANC care including IPTp treatment as per local/national guidelines.

#### 4.1. Inclusion Criteria

Subject eligibility should be reviewed and documented by an appropriately qualified member of the investigator's study team before that subject is included in the study. Subjects must meet all of the following inclusion criteria on Day 0 at Visit 1 to be eligible for enrollment into the study:

1. Pregnant women (all gravidae) with  $\geq 14$  and  $\leq 26$  weeks of gestational age (defined by ultrasound).
2. Evidence of a personally signed and dated informed consent document indicating that the subject (or a legally acceptable representative if a subject is  $< 18$  years of age) has been informed of all pertinent aspects of the study and that all questions by the subject have been sufficiently answered. Assent will be obtained from subjects  $< 18$  years of age.
3. Subjects who are willing and able to comply with scheduled visits, treatment plan, laboratory tests, and other study procedures.

4. Subjects who agree to be supervised for treatment administration, and are available for all follow up visits as per protocol, including follow ups at delivery and on 28 days post delivery.

#### **4.2. Exclusion Criteria**

Subjects presenting with any of the following will not be randomized in the study:

1. Age <16 years old or >35 years old.
2. Multiple gestations (more than one fetus) as per the ultrasound results at screening.
3. Clinical symptoms of malaria.
4. Hemoglobin < 8 g/dL (measured at baseline).
5. Any condition requiring hospitalization or evidence of severe concomitant infection at time of presentation.
6. Use of antimalarial drugs in previous 4 weeks.
7. History of convulsions, hypertension, diabetes or any other chronic illness that may adversely affect fetal growth and viability.
8. Inability to tolerate oral treatment in tablet form.
9. Known allergy to the study drugs (AZ, CQ, and SP) or to any macrolides or sulphonamides.
10. Present history of smoking or alcohol or drug abuse since first becoming aware of current pregnancy.
11. Participation in other studies within 30 days before the current study begins and/or during study participation.
12. Inability to comprehend and/or unwillingness to follow the study protocol.
13. Concurrent participation in another investigational study.
14. Previously randomized in this study.
15. Requirement to use medication during the study that might interfere with the evaluation of the study drug (eg, trimethoprim-sulfamethoxazole use in subjects positive for HIV infection) or is contra-indicated during pregnancy per package inserts.

16. Severe acute or chronic medical or psychiatric condition or laboratory abnormality that may increase the risk associated with study participation or investigational product administration or may interfere with the interpretation of study results and, in the judgment of the investigator, would make the subject inappropriate for entry into this study. Examples would include but not limited to:
  - a. Symptomatic HIV infection, including physical findings that suggest immunocompromised status (eg, oral candidiasis);
  - b. Neurological conditions which may predispose to complications during pregnancy, including seizure disorders;
  - c. Severe psychosis or major disorder that may interfere with the conduct of the study or adherence to study medication;
  - d. Known, clinically significant pre-existing renal or hepatic disease.
17. Evidence of current obstetric complications that may adversely impact the pregnancy and/or fetal outcomes, including presence of congenital anomalies, placenta previa or abruption.
18. Known severe sickle cell (SS) disease or sickle-hemoglobin C (SC) anemia.
19. Known family history of prolonged QT Syndrome, serious ventricular arrhythmia, or sudden cardiac death.

#### **4.3. Randomization Criteria**

A computer-generated randomization list will be provided by the sponsor to the investigators. Randomization will be stratified according to gravidae (primigravidae & secundigravidae vs. other gravidae). Among all gravida, approximately 50% subjects will be stratified with primigravidae & secundigravidae. The investigator will assign subject identification numbers sequentially as they are determined to be eligible for treatment (PID numbers). This unique PID number will be retained throughout the study and must appear on all case report form (CRF) pages, source documents and lab data. The eligible subjects who have met all inclusion/exclusion criteria will receive study medication assigned to the next available randomization number at the Day 0 during the first study visit. The randomization number will also be recorded on the proper CRF page.

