### 5.1. Allocation to Treatment

The investigator's knowledge of the treatment must not influence the decision to enroll a particular subject or affect the order in which subjects are enrolled. Refer to Section 4.3 (Randomization Criteria) for details.

090177e1811dafca\Approved\Approved On: 22-Feb-2010 14:41

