## 5.2. Breaking the Blind

The study is open label. However, the microbiologists (microscopists) will be blinded to the study treatments of the subject and the reading of other microscopists. The lab scientists undertaking the laboratory investigations (ie, molecular assays, biochemical assays, histological and microbiological investigations) will be unaware of the study group from which the sample was obtained.

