## 9.2. Efficacy Analysis

The primary efficacy analysis population (ie, Primary Analysis Set) will be intent-to-treat (ITT) for all endpoints. It will consist of subjects who are randomized, have received at least one dose of study medication (Day 0 at Visit 1 is considered the first dose of study medication), and have a single fetus. Subjects without the required data needed to compute an endpoint will be treated as missing. Analyses will also be performed for as per protocol analysis set, considered secondary. A per protocol analysis set will consist of all ITT subjects who have been compliant with study medication and will exclude subjects who have a neonate birth-weight measured greater than 7 days after birth if they do not already meet the definition of sub-optimal pregnancy outcome, and also exclude subjects who withdraw from study drug and switch to standard of care IPTp treatment. Compliance with study medication will consist of at least 6 of the 9 AZCQ daily doses, and at least 2 of the 3 SP daily doses. Once again, subjects without the required data needed to compute an endpoint will be treated as missing. Sensitivity analyses will be defined for both the ITT and PP populations.

Treatment group comparisons for the primary endpoint will use an overall alpha level of 0.00125 2-sided (equivalent to 0.000625 1-sided), subject to the alpha spending function specified in Section 9.5. Treatment group comparisons for the secondary endpoints will use an overall alpha level of 0.05 2-sided (equivalent to 0.025 1-sided), also subject to the same alpha spending function.

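### Section 4.3 gives the randomization list to the investigators of an open-label trial and describes no concealment, so the next allocation may be foreseen at enrolment

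*Protocol*

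**What the plan says.** Protocol Section 4.3 (Randomization Criteria): "A computer-generated randomization list will be provided by the sponsor to the investigators". The investigator numbers women in sequence as they are found eligible, and each eligible woman "will receive study medication assigned to the next available randomization number at the Day 0 during the first study visit". Stratification is by gravidity in two levels.

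Section 5.1 (Allocation to Treatment) consists of an instruction and a cross-reference: "The investigator's knowledge of the treatment must not influence the decision to enroll a particular subject or affect the order in which subjects are enrolled", followed by "Refer to Section 4.3 (Randomization Criteria) for details". Section 4.3 contains no concealment step to refer to.

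Section 5.2: "The study is open label. However, the microbiologists (microscopists) will be blinded to the study treatments of the subject". Laboratory scientists are also kept unaware of study group. Staff who enrol, dose and follow the women are not.

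Sections 4.1 and 6.1.1 set an order: consent, eligibility reviewed and documented, then randomization and first dose on Day 0. Section 5.3.1 supplies AZCQ in unit-dose bottles and Fansidar in its commercial container with an added label, so the packaging hides nothing. The protocol describes no central system, sealed envelopes, coded supply or separate holder of the list.

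**The concern.** Randomization protects the comparison only if whoever decides on entry cannot foresee the arm. Here the list goes to the investigators, numbers are used in sequence, and the only stated counter-measure is an instruction whose wording assumes that the investigator may know the treatment.

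There is room to act on such knowledge. Willingness and ability to comply, availability for all follow-up visits (Section 4.1) and exclusions 12 and 16 (Section 4.2) are matters of judgment. The 14 to 26 week entry window lets a woman be deferred. The arms differ in burden, since each AZCQ course needs two supervised home doses and SP needs none. Loss to follow-up and missing birth weight both count as primary events (Section 9.2.1), so steering by expected follow-up would act directly on the primary endpoint.

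The stratified analysis balances and adjusts for gravidity only. Imbalance in gestational age, health or likelihood of follow-up would remain. The study is described as the pivotal one for registration, and bias from selective entry cannot be reliably removed at analysis.

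**Working it through.** **Inputs.** One-sided alpha 0.000625, power about 90%, looks at 50%, 70% and 100%, gamma(-4) alpha spending and non-binding gamma(-6) beta spending (Section 9.5). Relative risk 0.80, with N set at the upper limit of each interval as the SP rate (Section 9.1, Table 4). The open top interval has no upper limit; 0.44 is assumed, from the last row of Table 5.

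**Step 1: reproduce Table 4.** With q = 0.8p, the fixed-design total on the log risk ratio scale is

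N = 2 × (3.227 + 1.282)² × [(1−p)/p + (1−q)/q] / (ln 0.80)².

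The spending functions give efficacy bounds Z = 3.793, 3.652 and 3.283 and a sample-size inflation factor of 1.0237.

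| SP rate | Fixed N | × 1.0237 | Table 4 |
|---|---|---|---|
| 0.28 | 4928 | 5045 | 5044 |
| 0.32 | 4108 | 4206 | 4206 |
| 0.36 | 3470 | 3553 | 3552 |
| 0.40 | 2960 | 3030 | 3030 |
| 0.44 | 2542 | 2603 | 2602 |

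Agreement is within one subject, so the test and boundaries used below are the plan's own.

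**Step 2: selective entry favouring AZCQ, no drug effect.** Let SP women have risk p and AZCQ women q = p − s, with s due to selection alone and n per arm. Then

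SE² = [(1−p)/p + (1−q)/q]/n, d = −ln(q/p)/SE, and a single final test gives P(false claim) = 1 − Φ(3.227 − d).

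Example with p = 0.28, s = 0.01, n = 2,522: SE² = (2.5714 + 2.7037)/2522, so SE = 0.0457; d = 0.0364/0.0457 = 0.795; P = 1 − Φ(2.432) = 0.75%. The three-look bounds give 0.71%.

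| Shift s | p=0.28, N=5,044: single test | three looks | p=0.44, N=2,602: single test | three looks |
|---|---|---|---|---|
| 0 | 0.0625% | 0.0625% | 0.0625% | 0.0625% |
| 1 point | 0.75% | 0.71% | 0.33% | 0.32% |
| 2 points | 5.2% | 4.9% | 1.4% | 1.3% |
| 3 points | 20.7% | 19.8% | 4.6% | 4.4% |

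The other rows of Table 4 fall between these two. The calculation covers the primary endpoint alone. It ignores futility stopping and the requirement that LBW also be significant for an early efficacy stop; both could only lower the rates.

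**Step 3: how large a shift would carry the result.** Solving d = 3.283 gives s = 4.1 points at p = 0.28 and 6.4 points at p = 0.44, a risk ratio of about 0.855 in both cases.

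**Step 4: the opposite direction.** With no drug effect, a 1-point shift against AZCQ at p = 0.28 cuts the false-claim rate to about 0.003%. With a true relative risk of 0.80 acting on an AZCQ baseline of 0.29, q = 0.232, SE = 0.0483, d = 0.188/0.0483 = 3.89, and single-test power is Φ(3.89 − 3.227) = 75%. Without the shift, q = 0.224, d = 0.2231/0.0489 = 4.56, and power is 91%.

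**Step 5: does the plan's simulation cover this?** No. Table 6 is run under equal true proportions in the two arms.

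**The case against.** **The protocol does not say that the next arm is visible.** A reader might infer that it is known before each woman is enrolled. The text does not go that far: it does not give the form in which the list is supplied or say whether the person judging eligibility holds it, and Sections 5.3.3 and 5.4 allow a designee or pharmacist to handle drug. This stands as a limit on the claim. It does not remove the point, because the wording permits foreknowledge and nothing in the protocol prevents it.

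**Some safeguards exist.** Consent and documented eligibility precede randomization, and gestational age, hemoglobin and age are objective criteria. This narrows the room for steering. The order of steps does not protect if the list is already in hand.

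**The direction and size of bias are unknown.** Staff worried about SP resistance could steer higher-risk women to AZCQ, which works against a superiority claim. The rate of 0.28 with N=5,044 is also the most sensitive row of Table 4. Both objections stand, which is why both directions and both ends of the table are shown.

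**The strict alpha might be said to give no protection against bias.** That is wrong. Putting 1.96 in place of 3.227 at p = 0.28, with d = 0.795, 1.599 and 2.411, gives false-claim rates of about 12%, 36% and 67%, against 0.75%, 5.2% and 20.7%. The threshold reduces the consequence of a shift without removing it.

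**The ITT definition might be thought to compound the problem**, since Section 9.2 says "It will consist of subjects who are randomized, have received at least one dose of study medication". Randomization and the supervised first dose fall at the same Day 0 visit, so few randomized women should go undosed. That is a separate, minor matter and carries no weight here.

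**Conclusion.** The point holds as a defect in a stated rule, and allocation concealment is a conduct rule that sites follow from the protocol. Sections 4.3 and 5.1 together permit foreknowledge of the next allocation and describe no concealment, so selective enrolment could bias the primary comparison in either direction.

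Under assumed shifts, a 1-point imbalance favouring AZCQ multiplies the one-sided false-claim rate about 5 to 11 times (0.32% to 0.71% against 0.0625%). Three points bring it to between about 4% and 20%, depending on the SP rate. A 1-point imbalance against AZCQ at an SP rate of 0.28 takes single-test power from about 91% to 75%.

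A reader might infer that selection could decide the trial by itself. For the expected result to reach the final boundary with no drug effect, it would need roughly 4 to 6 points. That is possible, but nothing in the documents makes it a prediction.

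**What to change.** Reword Section 4.3 so that the randomization list is withheld from everyone who screens, consents or enrols women, and state who holds it. Each allocation is released only after consent and eligibility are irrevocably recorded, by central phone or web randomization or by sequentially numbered opaque sealed envelopes. Reword Section 5.1 to describe that mechanism in place of relying on an instruction. If concealed allocation was always intended, the current sentence still has to change, because it says otherwise.

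The change should be in place before the first woman is enrolled. It alters neither sample size nor alpha. The cost is a paragraph of protocol text, the set-up of a phone, web or envelope system, and minor site logistics.

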#### **4.4. Life Style Guidelines**

Subjects will be encouraged to stay within the area during the entire pregnancy period and deliver in the hospital setting. Subjects will be encouraged to use LLINs. Site staff will discuss with subjects about the plan of hospital delivery. In case of home delivery, the subject will be asked to contact the study sites and report delivery within 24 hours of delivery. Fieldworker should visit the subject at home within 2 days of subject reporting delivery, and collect and/or transcribe data required in the study. If the site has not been notified of the delivery within 3 days post subject's due date, the study site will follow up with the subject about the delivery.

## 5. STUDY TREATMENTS

The Study treatment is a fixed dose tablet formulation of AZ and CQ (AZCQ) containing 250 mg AZ and 155 mg CQ base. Comparator drug is SP and will be supplied as Fansidar® (Roche) tablet (500 mg sulfadoxine/25 mg pyrimethamine). Subjects will be randomized in 1:1 ratio to receive either AZCQ or SP IPTp regimens. Both regimens will consist of three treatment courses. The treatment courses of AZCQ and SP will consist of the following:

1. **AZCQ treatment course:** 1000 mg AZ and 620 mg of CQ base (4 combination tablets of AZCQ with individual strength of 250 mg/155 mg), by mouth (PO) once daily for 3 days (Days 0, 1, 2);

OR

2. **SP treatment course:** 1500 mg sulfadoxine and 75 mg pyrimethamine (3 fixed tablets of SP strength at 500 mg/25 mg), PO single dose once daily on Day 0.

Each subject will receive three IPTp treatment courses of AZCQ or SP during ANC visits at 4 - 8 week intervals. The first treatment course will be administered during the second trimester (14-26 weeks of gestation as confirmed by ultrasound). The last treatment course should be given to subjects prior to or during 36 weeks of gestation.

The first dose of each AZCQ treatment course will be administered under supervision during the ANC visits. Subsequent two doses of AZCQ will be administered at home under supervision by the fieldworker(s).

Each dose of SP treatment will be administered under supervision during the ANC visits.

Please note that the terms course and dose are often used synonymously in IPTp studies using SP because only one directly observed dose is required per treatment course. Within this protocol, dose represents medications taken on a given day; course means all medications required for a complete treatment at one visit.

